### Participants

PCa survivors will be eligible if they (1) are AA or Hispanic men, (2) have clinically localized PCa diagnosed within 5 years prior to study enrollment, (3) are eligible to undergo AS or currently undergoing AS, (4) enroll with a spouse or intimate partner, (5) are ready and able to be physically active, as determined by a physician, (6) do not meet physical activity guidelines (i.e., 150 min of moderate physical activity or 75 min of vigorous physical activity), (7) have internet access at home (or at community center or church), and (8) have a valid home address and phone number.

PCa survivors will be excluded if they (1) have an active noncutaneous malignancy at any site; (2) had prior radiation therapy for treatment of the primary tumor; (3) have planned concomitant immunotherapy, hormonal therapy, chemotherapy, or radiation therapy during the study period; (4) participated in formative interviews for the study; and (5) participate in another physical activity, diet, or lifestyle program. Partners are eligible if they (1) are adults (≥ 18 years old) and (2) are ready and able to be physically active, as determined by a physician. The survivor-partner dyads can be married or unmarried, as well as same-sex or heterosexual. If one dyad member chooses to withdraw from the study, the other member will also be asked to withdraw from the study.

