### Recruitment and data collection procedures

A total of 40 dyads (i.e., 80 individuals) will be recruited and randomly assigned to either intervention (*n* = 30 dyads) or control arm (*n* = 10 dyads). Participants will mainly be recruited from the MD Anderson Cancer Center (MD Anderson) and Lyndon B. Johnson hospital in the Houston, TX area with collaborations with the Department of Urology at each site. Eligible participants will be retrieved from the hospital’s electronic health records. An invitation letter with urologists’ signatures will be sent to the survivors, and approximately 10 days to 2 weeks later, survivors will receive a call to be invited to the study. Study staff will explain the study, and only survivors who are interested will be screened for inclusion/exclusion criteria via telephone. To recruit partners, research staff will ask permission to contact partners via telephone to screen their eligibility. To facilitate enrollment of dyads, eligible survivors will be asked to come with their partners to MD Anderson. In particular, if survivors were treated at MD Anderson, our study visit will be scheduled on the same day as their follow-up appointment at MD Anderson. Thus, they will not need to come to MD Anderson again only to participate in our study. For all participants, we will cover their parking expenses.

In addition, we will recruit participants from the community with help from the Center for Community-Engaged Translational Research (CCETR; Director: [name]). CCETR is an institutional research resource for investigators that maintains relationships with over 70 local and national organizations, providing a platform to assist with identifying and developing partnerships with Houston-area community organizations. For interested persons who contact us by telephone, hear a detailed description of the study, and provide oral informed consent to be screened, they will be screened for the inclusion/exclusion criteria. Those ineligible will be thanked for their time, and those eligible will be scheduled for an in-person baseline visit. As the participants will be recruited from multiple sites, block randomization will be used to ensure the same number of participants in each arm from each recruitment site.

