#### Analytic plans

The intervention adherence rate for each dyad is defined as the proportion of intervention sessions completed by both the survivor and partner. We will look at percentage of both survivor and partner completing a minimum of 9 out of 12 coaching calls and both nutrition counseling sessions. Feasibility of recruitment will be achieved if ≥ 30% of eligible participants enroll in the study, and ≥ 80% participants complete follow-up assessments at months 3 and 6. Feasibility of intervention adherence will be achieved if average proportion of intervention adherence rate is ≥ 0.7 (e.g., coaching calls and nutrition sessions completed by both the survivor and partner ≥ 70%).

Linear mixed models will be used when combined data from both survivors and partners are analyzed due to their correlation within couples. The primary endpoint for the efficacy of the interventions is the differences between intervention and control group in outcome changes between baseline and 6 months post baseline. Specifically, an intervention indicator will be included and tested for the difference of increase in outcomes between groups. In our data, cluster corresponds to couples and random intercepts will be used to represent the pair effects. We will also conduct analysis of covariance to compare efficacy outcomes of interest pre and post intervention between intervention and control group separately for survivors and partners. Covariates and corresponding baseline outcome will be adjusted for in the analyses. Two-sided statistical tests will be performed, and the significance level for each test will be set at 0.05 without adjustment for multiple testing. All results from the statistical tests will be interpreted as hypothesis generating rather than conclusive findings. We will additionally perform various descriptive analyses, including dyadic analyses, to characterize the sample and compare participants and those who refused/withdrew on demographic and medical factors.

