### Sample Size Justification

Our sample size of 40 dyads provides adequate statistical support to help evaluate our primary aim of feasibility. In terms of evaluating feasibility based on recruitment, if the true consent rate of eligible dyads is 85%, then there will be 88% probability for us to screen 50 couples or less to arrive at 40 couples that consent; if the true consent rate is 75%, then there will be only 26% probability for us to screen 50 couples or less to arrive at 40 couples consenting. With the chosen total study sample size of 40 dyads, the randomization ratio would then be determined by the sample size chosen specifically for the intervention arm. With a lack of data available in the literature on the adherence of the proposed intervention among racial/ethnic minority PCa patients and partners, it would be valuable to allocate more patients to the intervention arm than the control arm to allow a more accurate assessment of the intervention adherence rate (as part of the primary objective of the study).

Specifically, when the sample size is 30, a two-sided 95% confidence interval (CI) for the average adherence rate will extend 0.36 standard deviation (SD) from the observed average rate, where SD is the estimated standard deviation of the adherence rate, assuming the CI is based on the large sample z statistic. This is in contrast to the corresponding half width of the 95% CI for the average adherence rate of 0.44 SD when the number of dyads in the intervention arm is 20 (as a result of a 1:1 randomization ratio), representing a less precise estimate of the mean adherence rate. Finally, we would like to keep a control arm with a reasonable number of patients (10 as chosen) to allow assessment of preliminary efficacy of the intervention with a reasonable level of accuracy, yet as a secondary objective of the study.

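### Asking the remaining dyad member to leave the study forgoes follow-up that the analyses can use and lowers measured retention; the pooled 80% criterion needs retention by arm reported beside it

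*Protocol article*

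**What the plan says.** The withdrawal rule is in the Participants section of the protocol article: "If one dyad member chooses to withdraw from the study, the other member will also be asked to withdraw from the study". It makes no exception for either arm and does not mention continued assessment of the member who is willing to stay.

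The retention criterion is in Analytic plans. Together with a recruitment threshold of 30%, feasibility requires that at least "80% participants complete follow-up assessments at months 3 and 6". No arm is named, and the unit as worded is the participant.

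The sample is set out under Recruitment and data collection procedures: "A total of 40 dyads (i.e., 80 individuals) will be recruited", with 30 dyads in the intervention arm and 10 in the control arm. The Sample Size Justification keeps 10 controls for preliminary efficacy, a secondary objective.

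Analytic plans gives two efficacy analyses. One is a linear mixed model with a random intercept per couple for the combined data. The other is an analysis of covariance to "compare efficacy outcomes of interest pre and post intervention between intervention and control group separately for survivors and partners".

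**The concern.** Ending joint coaching when a couple is no longer taking part together is one matter; ending assessment of the person who would stay is another. Follow-up is collected person by person: self-administered questionnaires, an accelerometer worn by each participant, and blood from the survivor only. Control dyads have no joint sessions at all. They receive a list of websites at baseline and the study materials after month 6.

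Two things are at stake.

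- **Missing data.** A survivor's month-6 outcome, blood included, may go uncollected because the partner left. Such a loss may be related to how the couple is doing, so it need not be random. With 10 control survivors, each one lost is 10% of that arm's marker data.
- **The feasibility verdict.** The 80% criterion belongs to the primary aim. Under the rule, one person's decision can count as two losses, so the measured figure partly reflects the procedure rather than willingness to stay.

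A separate weakness of the same criterion is that it pools over a 3:1 allocation. The control arm contributes only a quarter of the count, although a larger trial would need to know whether controls can be retained.

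**Working it through.** **Check on the plan's own figures.** The document gives no retention probability, but its recruitment probabilities use the same binomial tool and reproduce. P(at least 40 of 50 consent) is 0.880 at a consent rate of 85% and 0.262 at 75%; the document states 88% and 26%.

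**Inputs from the document.** 40 dyads (80 individuals), 30 and 10 by arm, threshold 80%. The threshold is 0.8 × 80 = 64 individuals, or 0.8 × 40 = 32 dyads.

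**Assumptions.** The document gives no dropout rate, so I take 10% individual withdrawal as the main case, with 5% and 15% as the range. Withdrawal is taken as the only reason for not completing, and under the rule every remaining member is taken to comply with the request. The results with the rule are therefore the largest effect it can have.

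**1. Can the analyses use one member?** The separate analyses of covariance use survivors' data for survivors and partners' data for partners. A model with a couple random intercept accepts a couple that contributes one member. Neither needs the pair to be complete.

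**2. A direct count.** Nine people withdraw, each from a different dyad.

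- Without the rule: 80 − 9 = 71, and 71/80 = 88.8%, a pass.
- With the rule: 80 − 18 = 62, and 62/80 = 77.5%, a fail.

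**3. Probability of meeting 80%.** Let q be individual retention and ρ the within-couple correlation of staying.

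- P(both stay) = q² + ρq(1 − q).
- With the rule, the criterion is met if at least 32 of 40 dyads stay: Bin(40, P(both stay)).
- Without the rule, it is met if at least 64 of 80 individuals stay, summing over 40 independent couples that keep 2, 1 or 0 members. P(exactly one stays) = 2(q − P(both stay)).

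| Individual withdrawal | ρ | P(both stay) | Pass, with rule | Pass, without rule |
|---|---|---|---|---|
| 5% | 0 | 0.903 | 0.987 | >0.999 |
| 10% | 0 | 0.810 | 0.655 | 0.998 |
| 10% | 0.5 | 0.855 | 0.884 | 0.990 |
| 10% | 1 | 0.900 | 0.985 | 0.985 |
| 15% | 0 | 0.723 | 0.180 | 0.916 |
| 15% | 0.5 | 0.786 | 0.507 | 0.872 |

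Under independence, expected retention with the rule falls below 80% once individual withdrawal exceeds 1 − √0.8 = 10.6%.

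**4. Pooling over the arms.** A pass needs 32 of 40 dyads, or the equivalent in individuals. It is reached with 30/30 and 2/10, with 28/30 and 4/10, or with 27/30 and 5/10. Total loss of the control arm gives at most 30/40 = 75% and fails. Taking the dyad as the unit, with retention of X ~ Bin(30, p₁) and Y ~ Bin(10, p₂), P(X + Y ≥ 32) is:

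- 0.845 at true retention 0.95 (intervention) and 0.50 (control);
- 0.598 at 0.90 and 0.50;
- 0.354 at 0.85 and 0.50;
- 0.279 at 0.95 and 0.20.

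**5. Would a per-arm gate help?** The gate would be at least 24/30 and at least 8/10 intact dyads. With the 81% intact dyads of the 10%, ρ = 0 case, it passes with probability 0.660 × 0.708 = 0.47. With 85.5% (ρ = 0.5) it passes with 0.866 × 0.833 = 0.72. Both are below the pooled figures under the rule, 0.655 and 0.884.

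**The case against.** **The dyad is the unit of this trial.** Survivors must enrol with a partner, all coaching calls include both members, and adherence counts sessions completed by both. Intact-dyad retention is therefore a sensible quantity. This stands, and intact dyads should be reported. It does not require that assessment of the remaining member stop.

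**The rule is conservative.** It can only lower measured retention, so it cannot produce a falsely favourable verdict. This stands. The harm is a possible false failure and avoidable missing data. The rule and the pooling act in opposite directions, and one does not correct the other.

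**The effect depends on assumed dropout.** It does. Withdrawal within couples is plausibly correlated, the effect shrinks as correlation rises, and it vanishes at 1.

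**Pooling matters mainly in unbalanced cases.** At true retention of 0.95 and 0.50 the true pooled figure is (30 × 0.95 + 10 × 0.50)/40 = 83.75%, so a pass is correct for the quantity named. A fuller document may also plan reporting by arm.

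A reader might infer two stronger conclusions, and neither is supported. The first is that the rule discards data already in hand. The document says only that the other member is asked to leave, and nothing says that collected data are deleted. The second is that 80% should be a pass/fail rule in each arm. The document sizes the control arm for a secondary objective. With 10 dyads such a gate is noisy: at true retention of 90% in both arms it lowers the pass probability from 0.985 to 0.906, and in the cases of step 5 it lowers it further.

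**Conclusion.** The point holds as a design weakness that is cheap to repair. The withdrawal rule puts future month-3 and month-6 data from willing members at risk, although the planned analyses can use those data. It can also turn 88.8% retention into as little as 77.5% against an 80% threshold. At 10% individual withdrawal it lowers the chance of meeting the criterion from 0.998 to 0.655 under independence and from 0.990 to 0.884 at correlation 0.5. These sizes rest on an assumed dropout rate and on full compliance with the request.

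The pooling point is true as arithmetic: the criterion can be met with up to 80% of control dyads lost. It calls for reporting by arm, not for a second gate. The data concern bears mainly on the secondary efficacy aim, whose results the document treats as hypothesis generating. The retention concern bears on the primary feasibility aim.

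**What to change.** - Change the rule in Participants so that, when one member withdraws, the other is invited to continue all assessments and stays in the analysis. Whether dyadic sessions continue is for the investigators to decide.
- State in Analytic plans that the 80% criterion is counted over individual participants, as it is already worded.
- Beside the pooled verdict, report retention by arm and for survivors, partners and intact dyads, each with a confidence interval. Do not add a per-arm 80% gate on 10 control dyads.

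The cost is protocol and consent wording and a few extra assessments. The by-arm intervals will be wide for the control arm, which is a reason to show them rather than to base a decision on that arm alone.

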### Intervention

A conceptual model that focuses on the role and influence of social relationships (i.e., the partner) will be used to guide this investigation (Fig. 2). There is no one theory that adequately explains the link between social relationships and health [28]. Although social cognitive theory [29] and social support theory have been used extensively for behavior change [30], these theories lack a focus on how individuals communicate with and influence one another. Interdependence theory is a dyad-level theory that emphasizes the outcomes experienced by both the agent and target of influence in a reciprocal fashion, by focusing on how influence and communication affect behavior [31, 32]. Therefore, the proposed model for this study is derived from these theories and is based on three key tenets: (1) social influence as a fundamental behavior change process, (2) interaction between personal factors (e.g., stress) and environmental factors (e.g., social support) to enhance behavior change, and (3) adequate levels of personal and environmental factors to initiate and maintain behavior change. We present format, goals, and behavior change techniques for each of our intervention components in Table 1.

**Fig. 2 Fig2:**
[figure not shown]
Conceptual model

**Table 1 Tab1:** Intervention components, format, goals, and behavior change techniques

Intervention components	Format	Goals	Behavior change techniques
Health coaching	▪ Biweekly telephone counseling with a licensed counselor	Provide support for each other to meet the physical activity and healthy eating goals	▪ Motivational interviewing ▪ Provide information on consequences of behavior to the individual ▪ Goal-setting ▪ Prompt review of behavioral goals ▪ Social support ▪ General communication skills training
Home-based physical activity program	▪ Exercise prescription ▪ Printed materials ▪ Power point slides (voices over) ▪ Activity tracker	Engage in 150 min of moderate or vigorous physical activity per week	▪ Goal-setting ▪ Action planning ▪ Barrier identification/Problem solving ▪ Provide rewards ▪ Time management ▪ Self-monitoring of behavior ▪ Relapse prevention
Nutrition counseling	▪ Twice (in-person and/or via telephone) counseling sessions with a registered dietitian ▪ Printed materials (prevent T2) ▪ Food intake record (via MyFitnessPal.com or on paper)	Improve an overall diet quality including eat 5 servings of fruits and vegetables, reduce red meat intake, reduce sweetened beverage, and eat whole grain	▪ Goal setting ▪ Provide feedback on performance ▪ Provide instruction on how to perform the behavior ▪ Self-monitoring of behavior

#### Dyadic telephone coaching

The health coaching component will incorporate Motivational Interviewing and other motivation-based techniques to enhance commitment to and intrinsic motivation for diet and physical activity. The underlying goal is to evoke and support intrinsic motivation, which will lead dyads to initiate and persist in behavior change and maintenance efforts, as well as enhance retention in the program. The coaching will also employ cognitive-behavioral techniques to improve self-efficacy and other problem-solving and coping skills. Each dyad will receive 12 telephone coaching calls, each lasting approximately 45–60 min, from a master’s level trained counselor. Coaching calls will occur biweekly over the 6 months. During telephone coaching sessions, the health coach will ask about physical activity levels and eating behaviors, monitor the dyad’s progress, provide feedback, assist in solving physical activity and healthy eating barriers, address health concerns, and discuss goals until the next session. The survivor and partner will set their own behavior goals and begin at their own pace. They will also be encouraged to set a common behavior goal (either physical activity or healthy eating) that they engage in together. However, the health coach will emphasize that it does not mean that all activities should be done together and address how to support each other (e.g., providing emotional and practical support and avoiding nagging). All calls will include both members of the dyad, given the non-sensitive nature of the topics (e.g., behavioral skills, diet, and physical activity) and the focus on social support and interdependence.

#### Home-based physical activity program

The home-based physical activity program is adapted from an existing, evidence-based intervention, Active Living After Cancer (ALAC) program developed for cancer survivors [33]. The ALAC program is a theory-based, in-person and group-based program that consists of 12 weekly sessions that cover goal setting, benefits, and barriers to physical activity, problem solving, rewarding yourself, time management, self-efficacy, social support, and behavioral maintenance. The sessions are held in the community and led by trained health educators with PowerPoint slides. Participants receive a workbook with information on cognitive and behavioral skills to increase physical activity, written exercises to practice these skills, and case examples of cancer survivors who have successfully made physical activity changes. In addition, participants engage in 10–15 min activities together (e.g., resistance training and stretching and Zumba) and discuss survivorship topics (e.g., nutrition, fatigue and emotional distress). The goal of our home-based physical activity program is to engage in at least 150 min of moderate or vigorous physical activity per week. The program will provide the physical activity workbook and PowerPoint slides with our health coach’s voices over them. The workbook and PowerPoint slides will be slightly modified to target PCa survivors, couples, and racial/ethnic minorities. Furthermore, each member in the dyad will receive an individualized exercise prescription based on their current level of physical activity and health status from an exercise physiologist that includes options for activity selection (e.g., walking or bicycle riding), duration (time spent engaging in activity, ~ 20–60 min), frequency (number of days per week), and intensity (low and moderate). Finally, participants will receive an activity tracker to facilitate self-monitoring and a resistance training band.

#### Nutrition counseling

Each dyad will receive two nutrition counseling sessions with a registered dietitian. The first session occurs approximately a week after the baseline assessment (via telephone or in-person), with the second occurring at the time of the dyad’s choice before month 3. Participants will discuss goals, objectives, lifestyles, and current dietary habits with the dietitian. The goal is to get participants to improve diet, such as eating at least 2.5 cups of fruits and vegetables per day and reducing processed meat and red meat intake. Participants will be encouraged to record their food intake via MyFitnessPal.com or on paper, which we will provide in a binder, to encourage self-monitoring. Participants will also receive seven selected materials, including tracking food, healthy shopping and cooking, understanding carbohydrates, and eating well away from home, from prevent T2, a type 2 diabetes prevention program from the Centers for Disease Control and Prevention.

### Control group

The dyads assigned to the control arm will receive a list of physical activity and healthy eating behavior resources (websites) at baseline. In addition, after completing the month 6 assessment, they will receive the same physical activity and nutrition materials that the intervention dyads received.

